### Testing the impact of the intervention

#### Child behaviors

We expect that children in the Minipally intervention condition will have better social behaviors -higher levels of prosocial behaviors’ and lower levels of opposition, hyperactivity, inattention and physical aggression disruptive behaviors- as compared to children in the waiting list control group in post-intervention. We will use multilevel models where the child’ behaviors in pre-intervention will be considered as a covariate. We will thus 1) account for initial variation in children’s behaviors, and 2) account for the nested structure of the data: children are nested in childcare’s group (i.e. *n* = 8 children per educators) and the childcare’s groups are nested in child care services (i.e. *n* = 1 to 4 groups of preschoolers per child care services).

### Stress regulation

We hypothesized that children receiving the Minipally program will have better levels of stress regulation (i.e. better diurnal salivary cortisol patterns) at the end of the 8 months intervention than children in the waiting list control group. To model the impact of intervention on preschooler’ stress level, we will use a growth curve model accounting for time variation in cortisol, as cortisol samples were taken three times a day (at the arrival to the CSS, midmorning and 30 min after the afternoon nap). We expect to find a significant difference between the mean slope of cortisol secretion between the intervention and the control group in post-intervention, but not in the intercept levels. Growth curve models also account for the non-independence of repeated measures by modeling multiple data points as nested within individuals, which further allows for missing data. This technic accounts for shared variance within subjects while modeling between-subject differences. The normality assumptions for all our potential covariates and models will be assessed using standard statistical methods and comparison of residual versus predicted plots and residual versus normal scores.

Note that prior to any impact analyses, we will examine the cortisol data for extreme values. Cortisol outliers will be winsorized at >3 standard deviations ud/dL to ensure that extreme values do not exert a disproportionate influence on analysis. Cortisol values have skewed distribution and therefore will be transformed using Log 10. A constant of 1 will be added to original concentration [Log 10 (concentration + 1)] to assure positive transformed cortisol data. We will then use univariate and multivariate models to assess several factors known to potentially affect cortisol secretion (e.g. general sleep, general health, medication) and control for them in later analyses.

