#### Levels of stress assessed by salivary cortisol collected by research assistant

Salivary cortisol samples were collected by research assistants three times during the CCS visit, at both pre and post intervention: 1) 30 min after the child’s arrival (between 7:30 and 10 am); 2) before lunch (between 10:30 and 12:00); 3) 30 min after waking from the afternoon nap (between 14:00 and 16:00). One ml of saliva was collected with a narrow cotton sponge (diameter: 8 mm) covered with a thin, perforated plastic film (sterile and packaged individually). The sponge’s elongated form allowed the research assistant to hold the other end of the cotton sponge with a sterile glove. The sponge was kept under the child’s tongue for a minute. Salivary samples were then stored at −20 °C until cortisol concentration determination. Laboratory analyses were performed using a high sensitivity Enzyme Immunoassay (Salimetrics, LLC from State college, PA, USA). The lowest limit of detection is 0.007 μg/dL, and all samples were assayed in duplicates.

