### Statistical analysis

#### Determination of sample size

The trial was designed to test whether the Minipally intervention was superior to the usual educational in terms of stress regulation and children’ behaviors. We used Heo’s statistical procedure for cluster randomized trial in our sample size estimation [33]. That is, we based our calculation on the expected mean number of groups within each child care centers –i.e. 2 groups per child care center. Recall that the CCS are our randomization units. Power calculation indicated that 19 child care services would allow to detect a medium size effect of the intervention on the selected outcomes, with 90% power at a 2-sided significance level of α = 5%. Our model can be stated as Y_ijk_ = β_0_ + δX_i_ + u_i_ + u_j(i)_ + e_ijk_; where Y_ijk_ is the post-intervention response of the i^th^ study participant in the j^th^ educator group nested the k^th^ child care services, β_0_ correspond to baseline value of our primary outcome, δX_i_ assess the main effect of the intervention (where X = 0 for waiting list group and X = 1 for the experimental group), and the last three terms are random effects at every level of the trial analysis [33].

Data will be analyzed per the intention-to-treat principle where all participants are considered within their assignment group regardless of the number of Minipally sessions they received. Every child whose parents consented to the evaluation will be included for analysis if they completed at least one assessment (i.e. pre or post-intervention).

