### Data analysis

#### Testing the equivalence of the intervention and control groups at baseline

We will compare the intervention and control groups on a wide range of family, health and child variables assessed at pre-intervention to test whether the randomization procedure was successful in yielding equivalent groups. This is a first step in examining the extent to which biological and behavioral impacts observed in post-intervention are associated with the Minipally intervention, and not to confounding differences at baseline between treatment groups. Specifically, group differences will be examined for socio-demographic information (age, income and education of the parents, household composition); child variables such as the rates of disruptive behaviors; and CCS related variables such as number of hours attending child care services per week, number of months attending a child care service. If differences are detected, these variables will be statistically controlled for in subsequent analyses.

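### Pre-intervention cortisol has no stated role in the cortisol analysis, although it is sampled on the same schedule and baseline is a covariate for the co-primary behaviours

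*Protocol article*

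**What the plan says.** Child behaviours and stress are both primary outcomes (protocol article, Objectives). Cortisol is sampled "three times during the CCS visit, at both pre and post intervention" (Levels of stress section).

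The Stress regulation section describes a growth curve in which time is the time of day, over three samples. It expects the arms to differ in the "mean slope of cortisol secretion between the intervention and the control group in post-intervention" and not in intercept. The adjusters it names are "factors known to potentially affect cortisol secretion (e.g. general sleep, general health, medication" and the like. Cortisol at T1 (October) does not appear as a covariate, an occasion or an interaction.

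For the behaviours, the Child behaviors section says that the child's "behaviors in pre-intervention will be considered as a covariate", in order to allow for initial differences between children.

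The section on baseline equivalence lists socio-demographics, CCS attendance and "child variables such as the rates of disruptive behaviors". A variable is controlled for only if a difference between arms is found.

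The sample-size section prints a model in which Y "is the post-intervention response of the" participant, and says that the intercept β₀ should "correspond to baseline value of our primary outcome". It also includes every consented child "if they completed at least one assessment (i.e. pre or post-intervention".

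**The concern.** The two primary outcomes have the same pre-post design, but baseline adjustment is stated for only one of them. This is hard to put down to condensation, because the article specifies the cortisol analysis down to the winsorising limit and the constant in the log transformation.

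The β₀ remark does not fill the gap. β₀ is one fixed intercept, with no child index and no coefficient on a T1 measurement. The equivalence check does not fill it reliably either. Even if cortisol were checked, a test with 19 clusters has limited power, and the primary model would then depend on its result.

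With so few CCS, the arms can start with different diurnal slopes by chance. If the analysis uses T2 alone, the part of that difference that persists to T2 is read as programme effect or hides one. Any precision available from T1 is also given up.

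**Working it through.** **The plan's own figure.** The article claims 90% power with 19 CCS for a medium effect. It gives no ICC and no numeric effect, so the figure cannot be strictly reproduced. Taking 0.5 SD as medium, with 2 groups of 8 children per CCS and one common ICC, 90% is reached at an ICC of about 0.054 (normal) or 0.040 (t, 17 df). The point below does not depend on this.

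**Inputs from the article.** 10 and 9 CCS; 362 children, so 362/19 = 19.05 per CCS.

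**Assumed, because the article gives neither.** ICC 0.05 to 0.10, at CCS level only; T1-T2 correlation r of 0.2 to 0.6. The calculation treats the slope as a generic child-level measure in SD units and uses all 362 children.

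**Step 1: chance imbalance at T1.**
Design effect DE = 1 + (19.05 − 1) × ICC. SE of the arm difference = √[DE/19.05 × (1/10 + 1/9)].
- ICC 0.05: DE = 1.90; SE = √(0.0999 × 0.2111) = 0.145 SD. P(|difference| > 0.2) = P(|Z| > 1.38) = 0.168.
- ICC 0.10: DE = 2.81; SE = √(0.1472 × 0.2111) = 0.176 SD. P(|difference| > 0.2) = P(|Z| > 1.13) = 0.257.

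**Step 2: what carries into T2, and what adjustment gains.** The expected shift in a T2-only estimate is about r × imbalance. Adjustment multiplies the variance by about 1 − r². Power after adjustment, starting from 90%, is Φ[(1.960 + 1.282)/√(1 − r²) − 1.960]; the 80% column uses 0.842 in place of 1.282.

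| r | shift from a 0.2 SD imbalance | variance factor | from 90% power | from 80% power |
|---|---|---|---|---|
| 0.2 | 0.04 SD | 0.96 | 91.1% | 81.6% |
| 0.4 | 0.08 SD | 0.84 | 94.3% | 86.4% |
| 0.5 | 0.10 SD | 0.75 | 96.3% | 89.9% |
| 0.6 | 0.12 SD | 0.64 | 98.2% | 93.8% |

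**Step 3: simulation check.** CCS means were simulated 20,000 times per scenario, with 10 against 9 CCS, 16 children each, ICC 0.05 or 0.10 and no true effect. CCS-level correlations were 0.2 to 0.7 and child-level correlations 0.1 to 0.5. In the runs where the baseline difference exceeded one SE in a given direction:
- the T2-only estimate was shifted on average by 0.040 to 0.154 SD;
- the baseline-adjusted estimate was shifted by −0.005 to 0.001 SD.

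Over all runs at ICC 0.10, adjustment reduced the SE from 0.181 to 0.156 or 0.161 at the higher correlations. At low correlations it did not help: 0.181 became 0.183 (ICC 0.10) and 0.153 became 0.155 (ICC 0.05).

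**The case against.** The Stress regulation section is silent on T1 cortisol; it does not exclude it. The words about the post-intervention slope state an expectation and are not a model equation. A model using both occasions would also test the slope difference at T2. Other parts of the article point towards pre-post use:
- the abstract says that stress levels are compared at pre and post;
- the Design section calls the method pre-post;
- the analysis set admits children with only a T1 assessment, who cannot enter a T2-only model;
- the β₀ wording suggests a loosely expressed intention to use baseline.

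The child variables in the equivalence check are given as examples, so cortisol could be among them. The T2-only estimate is also unbiased on average, and its SE already includes chance imbalance.

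All of this stands, and it limits the claim. A reader might infer that the sponsor decided to discard T1 cortisol, and the article does not say so. What remains is that no sentence puts T1 cortisol into the cortisol analysis, while the behaviour section does so explicitly for its outcome. A check that might cover cortisol, and that adjusts only after a detected difference, does not replace a prespecified baseline term.

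**Conclusion.** The point holds as a gap in specification with a modest statistical cost. As written, the cortisol test is a post-intervention slope contrast in which T1 cortisol has no stated role.

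Two stronger readings are not supported. The randomised comparison is not biased by omitting T1; what is lost is protection in the trial actually drawn and, depending on r, efficiency. A material imbalance is also not likely: above 0.2 SD it has a probability of about 17% to 26%, and only about r times it reaches the T2 estimate, so 0.04 to 0.12 SD for a 0.2 SD imbalance against an assumed 0.5 SD effect.

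Protection against imbalance is the firmer ground. The precision argument depends on r for the cortisol slope, which the article does not give. The gain is negligible at r of 0.2 or less and material from about 0.4 to 0.5. All sizes rest on the assumed ICC and r.

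**What to change.** State in the cortisol analysis that T1 cortisol enters the model, and do not make this conditional on a baseline test.

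The preferred form is one growth model of the T1 and T2 samples with occasion × time of day × arm. T1 trajectories are constrained equal across arms, and there are random effects for child, group and CCS. The primary test is arm × time of day at T2. Randomisation justifies the constraint, because T1 precedes the intervention. Children sampled only at T1 or only at T2 then both contribute, in keeping with the stated analysis set.

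An acceptable alternative is T1 cortisol level and slope as prespecified covariates. That version needs a rule for children with no T1 saliva.

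The sample-size section should also be reconciled: either show a baseline term in the printed model or stop describing β₀ as the baseline value.

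The cost is a slightly more complex model. No new data are needed. If the T1-T2 correlation proves low, little precision is gained.

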### Randomization and masking

CCS were randomly assigned in a 1:1 ratio to either the Minipally intervention in year 1 or waiting list control using a computer-generated randomization sequence. In accordance with PROBE methodology, the team of investigators, including Research Assistants (RAs), was blind to the assignment of the CCS in the two conditions during the study. However, CCS directors, educators as well as parents were aware of group membership after randomization, as per the open-label design.

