### Procedure and measures

Outcomes were assessed during two visits to the CCS – one at pre (T1 in October) and one at post intervention (T2 in June). A team of two trained research assistants, blinded to intervention assignment status of the CCS, was present early in the morning (approximately 7 h30 am) to collect the first cortisol sample of the day (30 min after arrival at CCS), and to give the behavioral and general health questionnaires to parents at CCS arrival. Research assistants stayed all day at CCS to perform the different assessments until the last cortisol sample was taken (i.e. 30 min after the nap, at about 14 h–16 h). Research assistants also asked the educators to complete behavioral questionnaires about every child in their group. All the outcome measures and their times of assessment are presented below and in Table 1.

**Table 1 Tab1:** Summary of instruments used in the Minipally study

Outcome measures			
Concepts	Type and Source of measure	Instrument	Time of assessment
Primary outcomes			
Child Behaviors	Questionnaire, rated by childcare’ educators Questionnaire, rated by parents	Child Behavior Questionnaire (BEH, 24)	Pre and post-intervention
Opposition			
Hyperactivity			
Prosociality			
Inattention			
Agression			
Child’ agressive and prosocial behaviors	Observed and rated by research assistant	Observational tool designed for the study	Pre and post-intervention; at Child Care Services
Stress	Salivary cortisol, collected by research assitant	Biological samples	Pre and post-intervention; at Child Care Services
			Child Care Arrival (7 h30-10 h)
			Before Lunch (10 h30-12 h)
			30 min after napping in the afternoon (14 h–16 h)
Secondary outcomes			
Educational interactions with the children	Observed and rated by research assistant	Caregiver Interaction Scale (29)	Pre and post-intervention; at Child Care Services
Severity			
Detachment			
Permissiveness			
Harshness			
Educator’s behaviors with each child	Questionnaire, rated by childcare’ educators	Pacotis (30)	Pre and post-intervention
Potential confounding variables			
Sociodemographic information	Questionnaire, rated by child’ parents	Questionnaire designed for the study	Pre and post-intervention
Child’ General Health	Questionnaire, rated by child’ parents	Questionnaire designed for the study	Pre and post-intervention
Child’ Stressful Life Events	Questionnaire, rated by child’ parents	Stressful Life Event Questionnaire	Pre and post-intervention

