One of the main strength of this cluster randomized trial is its relatively large sample size (n CCS = 19, n children = 362) and the quality of the outcomes measurements (i.e. 3 cortisol samples per day in pre and post-intervention), as well as its multi-informant design to assess child social skills (i.e. observational data from research assistant, questionnaire from parents and child care’ educator). To our knowledge, no previous child care intervention study relied on an cluster experimental design (i.e. randomized child care services) to study social skills improvement and stress regulation among children. This design allows for both methodolical rigor and the respect of ethical RCT guidel﻿ines.

Several studies suggest that child care services of sufficient quality ﻿may be effective in promoting cognitive and social development, essential components of school readiness [2–4, 16]. A pedagogical program promoting social skills, if shown to improve social behaviors, would provide information on useful strategies to improve CCS. This knowledge is needed to identify how to best invest in early childhood, considering that early childhood investments present better returns compared to investments later in life [35].

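### The cortisol growth model names no educator-group or CCS level, so if implemented as written the primary slope comparison would ignore the unit of randomisation

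*Protocol article*

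**What the plan says.** The unit of randomisation is clear. Under Randomization and masking, "CCS were randomly assigned in a 1:1 ratio", and under Determination of sample size, "Recall that the CCS are our randomization units". The Abstract gives 10 intervention and 9 control CCS. Objectives lists cortisol as one of two primary outcomes.

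The two primary outcomes get different models:

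- **Child behaviors:** multilevel models that "account for the nested structure of the data", with children in educator groups and groups in CCS.
- **Stress regulation:** a growth curve model for the three samples taken in a day. Its stated feature is "modeling multiple data points as nested within individuals, which further allows for missing data". The section then speaks of variance within and between subjects. It names neither educator group nor CCS. The expected effect is a difference between arms in the mean post-intervention slope, with no difference expected in the intercept.

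Determination of sample size covers both outcomes. It gives one equation with three random terms, u_i, u_j(i) and e_ijk, said to represent every level of the analysis. The equation describes a single post-intervention response.

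**The concern.** The article describes the dependence structure of both primary models. It supplies the cluster levels for one, and only the repeated-measures level for the other. An analyst who follows Stress regulation literally would fit samples within child and compare slopes as if the children were independent units.

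They may well not be. "Outcomes were assessed during two visits to the CCS", so the children of a CCS provide their diurnal profile at the same visits, and they share the lunch and nap routine that times the second and third samples. If slopes differ between CCS for such reasons, a child-level analysis reads those differences as evidence about the arms. Confidence intervals become too narrow and the 5% error rate is lost on a primary outcome.

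**Working it through.** **Inputs from the article.** Discussion gives a "relatively large sample size (n CCS = 19, n children = 362", so the mean is m = 362/19 = 19.05 children per CCS. Allocation is 10 v 9 CCS (Abstract). Two groups per CCS are expected (Determination of sample size), with 8 children per educator (Child behaviors), which would give 16 per CCS.

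**Input assumed.** The article gives no ICC. Here the slope ICC is the share of the variance of children's estimated slopes that lies between CCS. The range used is 0 to 0.10.

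**The plan's own figure.** The article says that "19 child care services would allow to detect a medium size effect of the intervention on the selected outcomes"; the power claimed is 90%, for a two-sided test at the 5% level. It cannot be reproduced exactly, because neither the ICC nor a numeric effect size is given. Taking medium as d = 0.5:

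- Children per arm: 9 × 19.05 = 171.5 and 10 × 19.05 = 190.5.
- Design effect at ICC 0.05: 1 + 18.05 × 0.05 = 1.903.
- Standard error: √[1.903 × (1/171.5 + 1/190.5)] = 0.145, so d/SE = 3.44.
- Power: 93% by the normal approximation, 90% with t on 17 df. Without clustering it would be 99.7%.

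The stated 90% is therefore compatible with a calculation that allowed for clustering.

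**Error rate if clusters are left out of the slope test.** Design effect DE = 1 + (m − 1) × ICC; true two-sided error = 2 × [1 − Φ(1.96/√DE)]. At ICC 0.05, 1.96/√1.903 = 1.42, which gives 15.5%. The simulations used 8,000 trials per row, 19 CCS split 10 v 9, 362 children, three samples each and no true effect.

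| Slope ICC | DE | Child level, formula | Child level, simulated | CCS mean slopes, simulated |
|---|---|---|---|---|
| 0 | 1.000 | 5.0% | 5.1% | 5.4% |
| 0.01 | 1.181 | 7.1% | 7.4% | 5.2% |
| 0.02 | 1.361 | 9.3% | 9.0% | 4.8% |
| 0.05 | 1.903 | 15.5% | 15.7% | 5.5% |
| 0.10 | 2.805 | 24.2% | 24.6% | 5.2% |

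The first row was simulated with an intercept ICC of 0.10. CCS that differ only in cortisol level do not disturb the slope test.

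**Fewer children per CCS.** With 16, the formula gives 6.8%, 8.6%, 13.8% and 21.5% at ICC 0.01, 0.02, 0.05 and 0.10. With 15 and ICC 0.05, DE = 1 + 14 × 0.05 = 1.70 and the error is about 13%.

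**Would the sample-size equation repair it?** With equally spaced times −1, 0, 1, a child's slope is (third − first)/2. A CCS random intercept adds the same amount to both samples and cancels, so it cannot absorb between-CCS variation in slope. A small simulation agrees. A mixed model with a CCS random intercept and child random intercept and slope, but no CCS slope, rejected a true null in 38 of 150 trials at slope ICC 0.10. That is 25%, with a simulation margin of about ±7 points, in line with the child-level result.

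**The case against.** The strongest reply is that the article nowhere plans a child-level test. The sentence in Stress regulation explains why growth curves suit repeated and missing samples; it does not list every random effect. The sample-size section covers stress as well as behaviour, recalls that CCS were randomised and promises random effects at every level. Child behaviors describes the nesting as a property of the data. On this reading the cluster levels are understood, and random slopes and degrees of freedom belong in an analysis plan that is not shown.

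Much of this stands. A reader might infer that cortisol will be tested as though children had been randomised. The documents do not say so, because individuals are never called the only level. A reader might also infer that the equation has no CCS term, since the text defines i as the participant. That does not hold either: u_j(i) is a group nested in i, and an educator group cannot be nested in a child. In the equation i must be the CCS, and the verbal definitions of i and k have been swapped.

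What does not stand is that the sample-size section settles the matter. Its equation has no time-of-day term, so it is not the cortisol model, and its intercept-only cluster effects would not protect a slope. Nor is this mere silence left to an analysis plan: the article states a nesting for cortisol, and it differs from the one stated for behaviour.

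The numbers are also conditional. Children absent on the visit day could not be sampled (Evaluation' adherence) and parents could refuse assessment (Intervention' adherence), so 19 per CCS is an upper figure for cortisol.

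**Conclusion.** The concern holds as a defect of specification. The cortisol model as written omits the randomisation unit, and nothing elsewhere in the article supplies a cluster term on the slope that carries the hypothesis. If it is implemented as written, the two-sided error exceeds 5% whenever slopes vary between CCS: roughly 7% to 24% for slope ICCs of 0.01 to 0.10. This rests on an assumed ICC and about 19 sampled children per CCS; at slope ICC 0 there is no inflation.

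A reader might go further and conclude that a false claim of stress reduction is likely. The figures do not support that. They make such a claim more likely than the design intends: about half of the rejections fall in the favourable direction, so at ICC 0.05 the chance is about 7.8% (15.5%/2) instead of 2.5%. Since this governs the validity of a primary test and is cheap to settle, it should be resolved before the cortisol analysis is run.

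**What to change.** State the cortisol model in Stress regulation as samples within child, within educator group, within CCS. Include a CCS-level random intercept and a CCS-level random time-of-day slope; the slope term is the one that protects the test. Test arm by time of day with small-sample degrees of freedom suited to 19 clusters (Kenward-Roger or Satterthwaite, about 19 − 2 = 17). A comparison of CCS-level mean slopes serves the same purpose and kept the error between 4.8% and 5.5% in the simulations.

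In Determination of sample size, correct the swapped definitions of i and k, so that the treatment indicator and the top random effect are plainly at the CCS.

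The cost is wording and model code, with no change to data collection. Confidence intervals for the cortisol effect will widen where slopes vary between CCS, as they should.
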